### Study monitoring and data safety monitoring

The study will be monitored using SMART-TRIAL. Before beginning the clinical trial, all centers will have a web-based meeting with presentation providing a description of the study, study procedures, and documentation. During the study period, monitors will have regular telephone contact with the participating departments to ensure the trial is conducted in compliance with the protocol and applicable regulatory requirements. Monitoring will be conducted according to risk-based monitoring and a study-specific plan by personnel not otherwise involved in the study. An independent Data Monitoring Committee will not be used as this is considered a low-risk intervention.

Adherence to protocol will be continuously monitored and the responsible centers notified of violations. Based on previous research and our pilot study, we have no reason to expect negative side effects or interactions with bilberries or oats. Therefore, an interim safety analysis will not be conducted. Any side effects of the bilberry, oat or reference/placebo products will be registered according to 7b World Allergy Organization Subcutaneous Immunotherapy Systemic Reaction Grading System embedded in the eCRF.

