**Discussion:**

Controlling hyperlipidemia and inflammation is critical to preventing new cardiovascular events, but novel pharmacological treatments for these conditions are expensive and associated with negative side effects. If bilberry and/or oat, in addition to standard medical therapy, can lower LDL cholesterol and inflammation more than standard therapy alone, this could be a cost-effective and safe dietary strategy for secondary prevention after AMI.

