A meta-analysis of more than 50 clinical trials concluded that oats can lower LDL cholesterol by 5–8% [16], and subsequent data suggest other anti-atherogenic properties of oats, including reducing inflammation and oxidative stress [17]. Recent studies indicate that bilberries from Sweden, rich in polyphenols and anthocyanins, may have direct or indirect positive effects on cardiovascular risk factors [13, 18, 19]. It has been suggested that consumption of the anthocyanins present in bilberries may reduce risk of death from CVD [20–22], have beneficial effects on platelet function, increase high-density lipoprotein (HDL) cholesterol [23, 24], and improve exercise tolerance [25, 26]. The mechanisms of action of berries are likely to be different from those of oats, potentially providing additive or synergistic beneficial effects. We recently conducted a small open-label randomized clinical trial of bilberry supplementation in patients post-AMI receiving high-dose statin treatment and found significant beneficial effects on lipid profile and exercise capacity in patients receiving bilberry supplementation [27]. We are proceeding to conduct a large, randomized, placebo-controlled clinical trial to assess clinical impact.

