### Dietary intervention

Subjects will be randomized to one of the four dietary intervention arms initiated within 5 days post-PCI and continued for 3 months. After randomization, subjects will receive beverages with bilberry powder (active), beverages with high-fiber bioprocessed oat bran (active), beverages with bilberry and oats combined (active), or reference beverages containing no active bilberry or active oats, for consumption twice daily (160 kcal/day).

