The beverages will be balanced to ensure isocaloric conditions. Intake twice a day is considered appropriate given the relatively short elimination half-life of anthocyanins which are believed to be important for the hypothesized effect from bilberries. The study products are under development by food scientists at Glucanova (Lund, Sweden) in collaboration with Chalmers University of Technology, Gothenburg, Sweden. Dried bilberry powder is provided by Immun (Skellefteå, Sweden). The oat bran will be bioprocessed to enable production of a palatable oat bran drink. The daily dose of oat bran will be 50 g, providing approximately 9.5 g dietary fiber of which 5 g beta-glucans, as well as abundant potentially bioactive phytochemicals, such as the oat-specific polyphenolic avenanthramides. The daily dose of the active bilberry product will contain 40 g dried bilberry powder, equal to approximately 480 g of fresh berries. Bilberry powder contains multiple anthocyanins and other polyphenols [27], the levels of the specific batches used in the present study will be analyzed in the intervention products and reported at a later date. The quantity of bioprocessed oat bran and bilberry powder in the combined study product will be 50% that of the separate supplements. The four study products are designed with similar texture and to look and taste as if they contain both bilberries and liquid oats, to enable double blinding. The reference product is based on starch, collagen, corn oil, sucrose, and citric acid. Small amounts of starch, collagen and corn oil were also added to the dried bilberry drink and the bilberry + oats drink to ensure isocaloric conditions as well as similar nutrient profiles and sensory properties (Table 3). Subjects will be instructed not to consume foods containing bilberry other than the intervention products, and no more than 15 g of oatmeal, or the equivalent, per day, during the intervention. Dietary advice according to routine treatment after AMI will be given to all study subjects.

**Table 3 Tab3:** Nutritional content of study products

Nutrition (g/100g)	Dried bilberry drink	Bioprocessed oat bran drink	Bilberry + oat bran drink	Reference drink
Energy (kcal/100g)	32.1	32.7	32.0	32.3
Fat	0.6	0.9	0.9	0.7
- Of which saturated fat	0.1	0.2	0.1	0.1
Protein	0.9	2.0	1.4	1.3
Carbohydrate	4.8	3.3	3.7	5.3
- Of which sugars	3.0	2.0	2.5	2.2
Dietary fiber	1.8	1.9	1.9	0.0
- Of which β-glucan	0.0	1.0	0.5	0.0
Salt	0.06	0.05	0.00	0.02

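### The only side-effect method named is a scale titled for systemic reactions to injected immunotherapy, so non-allergic tolerability of the fibre-rich drinks may be poorly classified

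*Protocol article*

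**What the plan says.** Under Study monitoring and data safety monitoring, the article sets both the scope and the instrument of side-effect recording. The scope is "Any side effects of the bilberry, oat or reference/placebo products", and these "will be registered according to 7b World Allergy Organization Subcutaneous Immunotherapy Systemic Reaction Grading System", embedded in the eCRF. The same section expects little to record: "we have no reason to expect negative side effects or interactions with bilberries or oats". On that ground it plans no interim safety analysis, and it dispenses with an independent Data Monitoring Committee because the intervention is considered low risk.

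The products are drinks, supplied "for consumption twice daily (160 kcal/day") for 3 months (Dietary intervention). The daily oat dose is described as "providing approximately 9.5 g dietary fiber of which 5 g beta-glucans". Table 3 gives fibre in g per 100 g for the bilberry, oat, combined and reference drinks in that order: "Dietary fiber 1.8 1.9 1.9 0.0".

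Table 1 lists no tolerability or adverse-event endpoint. The Abstract closes with the prospect that, if LDL cholesterol and inflammation fall, "this could be a cost-effective and safe dietary strategy for secondary prevention after AMI". The main Discussion ends on a similar, equally conditional note.

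**The concern.** A grading scale helps only if its categories match the events likely to occur. A scale built for systemic reactions to injected immunotherapy is, judging by its title, aimed at allergic reactions. The events one would first look for with a daily fibre load taken by mouth are of another kind: digestive complaints, and intolerance that leads a patient to give up the drink.

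Three things are at stake. First, between-arm tolerability may be graded inconsistently across centres if staff must fit such complaints to an allergy scale. Second, intolerance would help to explain the roughly 15% dropout that the sample size section anticipates and the non-adherence that the Discussion lists as a limitation. It could also weaken the blinding if complaints cluster in the active arms. Third, the Abstract sets the dietary strategy against drugs that it describes as having negative side effects. A comparative message of that kind needs side effects recorded by a suitable method.

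**Working it through.** **Does the document name any other method?** The sentence in Study monitoring and data safety monitoring covers any side effect of any of the three kinds of product and names one system. No other adverse-event scale, form or grading method appears in the article. The mismatch is therefore a choice that the article states, not a detail left to a fuller document.

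**Do the arms differ in something that makes non-allergic effects plausible?** The inputs are 160 kcal/day (Dietary intervention) and the energy and fibre content per 100 g (Table 3).

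Amount of drink per day (g) = 160 ÷ (kcal per 100 g) × 100.
Fibre per day (g) = 160 ÷ (kcal per 100 g) × (g fibre per 100 g).

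| Drink | kcal/100 g | Fibre g/100 g | Drink g/day | Fibre g/day |
|---|---|---|---|---|
| Bilberry | 32.1 | 1.8 | 498 | 160/32.1 × 1.8 = 9.0 |
| Oat | 32.7 | 1.9 | 489 | 160/32.7 × 1.9 = 9.3 |
| Bilberry + oat | 32.0 | 1.9 | 500 | 160/32.0 × 1.9 = 9.5 |
| Reference | 32.3 | 0.0 | 495 | 0.0 |

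The plan's own figure is about 9.5 g/day for the oat arm. Table 3 gives 9.3 g, which agrees within rounding: at exactly 500 g/day, 1.9 × 5 = 9.5 g. The method therefore reproduces the stated figure. Each active arm exceeds the reference by about 9 to 9.5 g of fibre per day, and the three active arms lie within about 0.5 g of one another.

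**What else would show a tolerability problem?**

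- Laboratory and cardiac measures at baseline and 3 months: creatinine, cystatin C, HbA1c, NT-proBNP and troponin-I (Blood and fecal samples); ejection fraction (Transthoracic echocardiography); heart rate and blood pressure. None of these records digestive intolerance.
- Death, new AMI and unplanned revascularization from the registry at 1 year (Register follow-up). These are exploratory, and the Discussion says the trial is not powered for them.
- Counts of empty packages and unused drinks (Discussion). These can show by arm that intake fell, but not why.

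The eCRF side-effect record is thus the only stated record of product side effects, although it is not the only data with a bearing on safety.

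The document gives no rate for any side effect, so the number of events that might be misclassified cannot be calculated from it.

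**The case against.** The strongest reply has several parts.

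*Registration is not grading.* The text says that any side effect will be registered; the named system governs how. That stands. It does not follow that digestive complaints would go unrecorded, only that their classification is uncertain.

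*The scale itself is not shown.* Its items and grades are nowhere in the article, and the label 7b may point to a numbered form that is not at hand. That also stands: the mismatch is judged from the title alone, so it would be too much to say that non-allergic events have no valid grade.

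*Other safety data exist.* A reader might infer from the absence of a committee and of an interim look that the eCRF form is the trial's only safety evidence. The documents do not support this, given the laboratory, cardiac, registry and returned-product data.

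*There is no firm safety claim.* A reader might conclude that the trial cannot support its claim of safety. The wording in the Abstract and Discussion is conditional, and no safety hypothesis is listed, so that conclusion is too absolute.

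*The Background on platelets.* A reader might set the Background's remark that anthocyanins may "have beneficial effects on platelet function" against the expectation of no interactions and see a contradiction. It is not one. A tentatively suggested benefit is compatible with expecting no harmful interaction, and the article does not discuss bleeding.

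*General adverse-event items usually sit in the full protocol.* This is true of their detail, and a protocol version 2.0 exists that is not shown. It does not remove the point, because the article itself applies this one scale to all product side effects.

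**Conclusion.** The point holds in a limited form. The article fixes, for every side effect of an oral product, a scale whose title ties it to systemic reactions to injected immunotherapy, and it names nothing else. The active arms receive about 9 to 9.5 g more fibre per day than the reference, so non-allergic tolerability differences between arms are plausible and may be poorly classified. The conditional suggestion of safety is then weakly supported on tolerability, though not without any support.

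This rests on two assumptions: that the title describes what the scale is meant to grade, and that a fibre difference of this size can cause digestive effects. The article states neither. The primary LDL comparison does not depend on this record. The change is worth making because it is cheap and because nothing else in the stated plan would describe intolerance by arm.

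**What to change.** Keep the allergy scale for allergic reactions only. In the eCRF, record every adverse event as a term with a general severity grade, seriousness, relation to product and whether the product was stopped. Tabulate these by arm, with digestive complaints as a named category. If the full protocol already contains such a form, one sentence saying so would settle the matter. If the recording is left as it stands, limit the safety wording in the Abstract and Discussion to what an allergy-reaction scale and the planned laboratory and registry data can show.

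The cost is one eCRF form change, slightly more data entry at the sites and one safety table. No extra visits are needed, and the sample size and primary analysis do not change.

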## Discussion

In the BIOAMI study, we will investigate the potential cardiometabolic benefits of supplementation of standard post-AMI treatment with daily bilberry and/or oat intake. We will assess whether beverages with dried bilberry and/or bioprocessed oat bran lower lipid levels, reduce inflammation, and/or improve exercise capacity. Given the significant ongoing CVD burden in patients after AMI, there is a need for novel evidence-based strategies for safe secondary prevention. Diet alteration is a generally safe intervention, and international guidelines recommend diets high in fruits, vegetables, and whole grains [10]. The source of the cardioprotective effects of specific diets such as the Mediterranean and Nordic diet may be their high content of fruit, vegetable, and whole grains — foods rich in bioactive compounds and dietary fiber. Robust scientific evidence for clinical effects of specific foods is warranted and for the role of bioactive compounds that may mediate the effect. Bilberries and oats both contain phenolic compounds with potential lipid-lowering and anti-inflammatory effects [17, 23, 46]. The primary cholesterol-lowering effect of oats has been attributed to the viscous soluble fiber beta-glucans, and a cause-effect relationship has been established [16]. Other potential CVD prevention properties of oats may involve anti-inflammatory and antioxidant action as well as maintenance of endothelial function [47]. This has been suggested by in vitro and animal experiments with oat bran [48] as well as isolated oat-specific polyphenols (avenanthramides) [49–51].

Polyphenols from bilberries may affect exercise tolerance [25, 26], and, in prospective studies, a high intake of anthocyanins has been inversely associated with risk of AMI [52, 53].

Some previous trials conducted in at-risk populations have provided evidence of improved cardiovascular function following intervention with a Nordic diet that included bilberries and oats [11–13] and from daily bilberry consumption [54]. However, the potential benefit of bilberry and oat intake in patients with manifest CVD needs to be clarified in large clinical trials [15].

In contrast to previous smaller studies in at-risk populations, the proposed study is powered to evaluate clinically relevant effects on LDL cholesterol in patients following overt AMI. In addition, we will use untargeted metabolomics to detect potential biomarkers of responders and non-responders to the interventions and characterize gut microbiome/diet interactions, as well as to investigate how metabolic networks are affected by the interventions.

All AMI patients in our pilot study received statin therapy. Bilberry administration was initiated within 72 h of PCI during a vulnerable and critical clinical phase [55, 56]. Despite statin treatment, we found significant correlation of LDL cholesterol and oxidized LDL with blood levels of anthocyanins after an 8-week intervention, indicating a possible dose-response relationship of anthocyanins in bilberries with cholesterol levels. The lipid-lowering effect of bilberry could be partly explained by the high anthocyanin content [57]. Oxidized LDL is associated with all stages of atherosclerosis and with co-morbidities linked to CVD, such as diabetes mellitus, hypertension, and obesity [58]. We speculate that both bilberries and oats could play a role in supplementing medical therapy, but probably through different mechanisms, showing potential for cumulative or synergistic beneficial effects. Both bilberries and oats are natural foods that have shown potential for CVD prevention when provided separately, but their combined effects have not been studied in clinical trials nor have effects of bilberries or oats been studied in large populations with overt disease, as in this trial with 900 AMI patients. A synergistic effect of oats and bilberries could suggest development of novel cholesterol-lowering functional foods as a potential cost-effective and safe dietary strategy for reduction of cardiac risk after AMI.

In designing the intervention drinks, we faced a challenge regarding calorie intake. In order to balance the four intervention drinks calorie-wise and to avoid high contents of sucrose and starch content in the reference product, we designed the combined bilberry/oat drink to contain half the quantity of bilberry and oats in the separate drinks. Our study therefore does not fulfill 2 × 2 factorial design criteria, and this limits our ability to investigate possible interactions between bilberries and oats without making assumptions about the linear dose-response relationship.

Potential limitations also include non-adherence to the dietary regimen. However, the intervention products, developed by food scientists representing both the academic and food science fields (Chalmers University of Technology, Gothenburg, Sweden, and Glucanova, Lund, Sweden, respectively), are shelf-stable ready-to-use beverages with acceptable taste and freshness, containing natural ingredients. In order to assess compliance, we will compare polyphenolic metabolites in blood associated with bilberry and oat intake at baseline and at 3 months. Compliance with the intervention product intake will also be calculated from returned empty packages and unused drinks.

For safety reasons, baseline recordings of clinical exercise and muscle tests will not be conducted; the absolute values for changes in exercise capacity after AMI can therefore not be estimated. However, subjectively assessed physical activity will be evaluated at baseline and at 3 months using validated questionnaires. Our study is not powered to assess hard clinical endpoints such as death, new AMI events, or new unplanned revascularizations, but we will follow-up such events reported in registries at 1 year following randomization, as an exploratory analysis.

## Current trial status

The trial was registered on ClinicalTrials.gov on August 8, 2018 (ID NCT03620266). Enrolment will begin in September 2021 and is expected to continue for 2 years. All study sites are prepared to start inclusion of patients in 2021, with an amendment from the Ethical Review Board approved for inclusion of Sahlgrenska University Hospital Gothenburg and Karlstad general hospital. The final results of the primary endpoint are projected for August 2023. An open-label pilot study with 50 patients was conducted in 2014/2015 and reported in 2018 [27], and it resulted in some adjustments in the study protocol and design of the study with inclusion of oats and two more study arms, and development of the pilot product (dried bilberry powder), a liquid oat product, their combination, and a reference/placebo product for use in the intervention. Developed study products were of importance for achieving high compliance to the dietary regimen. The current protocol version is 2.0 and dated December 20, 2019.

## Data Availability

Data cannot be made freely available as they are subject to privacy in accordance with the Swedish Public Access to Information and Secrecy Act but can be provided to researchers upon request, subject to a review of privacy. Requests for data can be sent to the corresponding author.

## Abbreviations

AMI: Acute myocardial infarction
apo A: Apolipoprotein A
apo B: Apolipoprotein B
CVD: Cardiovascular disease
HbA1c: Glycosylated hemoglobin
HDL: High-density lipoprotein
hs-CRP: High-sensitivity C-reactive protein
IL-6: Interleukin 6
LDL: Low-density lipoprotein
Lp(a): Lipoprotein A
NSTEMI: Non-ST-segment elevation myocardial infarction
NT-proBNP: ProBrain natriuretisk peptid
PCI: Percutaneous coronary intervention
sdLDL: Small dense low-density lipoprotein
STEMI: ST-segment elevation myocardial infarction
TC: Total cholesterol
TGA: Triglycerides
